## Data collection and management

### Plans for assessment and collection of outcomes {18a}

Bladder diaries and the parents reported satisfaction of urinary symptoms questionnaire are distributed at the beginning of treatment on paper. The demographic data from each participant will be derived from the electronic medical record (EMR). All outcome data will be collected at the end of the 12 weeks treatment period and converted by the research assistant into a digital file. A standard frequency-volume chart with additional information of urinary incontinence episodes and urgency episodes will be used as bladder diary [10]. The parents’ reported satisfaction of urinary symptoms score is a non-validated 7 points Likert scale.

The following case report forms will be collected (see also Fig. 3 and Table 1):
-t1: First visit with the PS.

CRF with baseline patient characteristics: age, gender, presence of daytime urinary incontinence and/or enuresis nocturna, and comorbidities.

CRF with technical investigations: presence of urinary tract infection (yes/no), kidney ultrasound (US) (normal or abnormal), PVR on bladder US (ml), cystometric bladder capacity at uroflowmetry, and staccato pattern on uroflow suggestive for dysfunctional voiding (Y/N).

0: Second visit with the PS.

CRF with baseline daytime and nighttime diary parameters (volume intake, daytime diuresis, micturition frequency, AVV during the day, urgency episode (Y/N), number of urinary incontinence episodes, N of defecations, N of wet nights, nocturnal urine production, netto urine loss/night, presence of nocturnal polyuria), and parents’ reported satisfaction of urinary symptoms.

t1: First visit with the PT.

CRF with patient number, allocation group.

t2: Second visit with the PT, 6 weeks after ambulant treatment.

CRF with daytime and nighttime diary parameters after 6 weeks of treatment (same parameters as at visit 2 + averaged volume of 3 supervoids at 6 weeks) and parents reported satisfaction of urinary symptoms.

CRF with recorded (serious) adverse effects: the adverse event form.

*t3: Third and last visit with the PT, 12 weeks after ambulant therapy.

Same CRF’s as in t2.

CRF with treatment response (non-responder, partial responder, complete responder).

*t4: Third visit with the PT.

Same CRF’s as in t2.

CRF with the maintenance of treatment effect in partial and complete responders (in weeks).

### Plans to promote participant retention and complete follow-up {18b}

The short duration of the clinical trial (i.e., 18 weeks) should be the most important incentive to complete the whole trajectory. By inserting a follow-up visit in the middle of the study period, participants are promoted to continue the treatment protocol. Participants who discontinue treatment are no longer candidates to be included in part II of the TaPaS trial.

### Data management {19}

Data is entered manually in on an online firewall protected data registry on the password-encrypted server of the Ghent University. Subsequently, data will be stored in a central IBM SPSS database which is also protected by the institutional firewall. Only the trial coordinator has access to both data registries. To promote data quality, data will be controlled on impossible values by range checks.

### Confidentiality {27}

The participants’ data are pseudo-anonymized by assigning an unique code to every participant at the moment of inclusion to ensure confidentiality. Data will be stored during and after the trial in an online protected data registry and IBM SPPS database, only accessible by the trial coordinator and at the end of the study by the CI.

### Plans for collection, laboratory evaluation, and storage of biological specimens for genetic or molecular analysis in this trial/future use {33}

No laboratory examinations are performed; biological specimens are not to be collected.

### Statistical methods

#### Statistical methods for primary and secondary outcomes {20a}

Statistical analyses will be performed using SPSS version 25.0. Descriptive statistics of demographic characteristics will be presented by median and interquartile ranges (IQR) for continuous variables and frequencies and percentages for categorical variables. Since the small sample size, non-parametric tests will be chosen. In case a subject withdraws early, a new participant will replace them till the required sample size is reached. An ITT will be performed. If case data are missing, missing data will be imputed via multiple imputation.
° Intra-arm analyses (baseline vs. 12 weeks):Baseline and 12 weeks follow-up absolute values and absolute change and percentage change from baseline values will be presented as medians (IQR). Intra-arm analyses will be assessed using a two-sided Wilcoxon signed rank test.° Inter-arm analyses (sham versus TTNS therapy): differences in absolute and percentage change from baseline between both groups will be reported as medians (IQR) and will be presented with a 95% confidence interval.

Inter-arm analyses will be assessed using a two-sided the Mann-Whitney *U* test

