**Methods:**

Part I of the TaPaS trial is set up as a single-center randomized-controlled trial. Children, aged from 5 to 12 years with iOAB and/or nocturnal enuresis, are assigned to two groups by computer-generated randomization: TTNS therapy (intervention) and sham therapy (control). The primary outcome is the percentage difference in average voided volume (AVV) between baseline and after 12 weeks of treatment. Secondary endpoints are the percentage difference in supervoid volumes, number of urinary incontinence episodes/24 h and in voiding frequency, the difference in parent reported outcomes between baseline and after 12 weeks of treatment, and the duration of clinical response.

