#### Primary outcome

* To show that TTNS therapy is superior to sham therapy in terms of average voided volume (AVV).
The endpoint is the median change in baseline at 12 weeks in AVV, registered on the daytime bladder diary. The AVV is calculated by the sum of all voids during daytime (in ml) of 3 days in total divided by the frequency of voids during daytime over 3 days in total. We consider AVV as the most relevant variable to measure efficacy since it directly reflects the functional bladder capacity. Increasing the functional bladder capacity is the key of in OAB and/or nocturnal enuresis (in the absence of nocturnal polyuria) treatment. An increased bladder capacity should ultimately lead to a decrease in micturition frequency and in urinary incontinence episodes. The follow-up interval of 12 weeks was chosen since the effect of treatment can be expected after 12 weeks of treatment.

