### Sample size {14}

For the sample size calculation, an online software package was used:

Sealed Envelope Ltd. 2012. Power calculator for continuous outcome superiority trial. [Online] Available from: https://www.sealedenvelope.com/power/continuous-superiority.

The trial has a parallel superiority design. Based on the previous study by Patidar et al. [8], a mean difference of 20% in the primary outcome (i.e., percentage difference in AVV between baseline and after 12 weeks) between TTNS and sham can be expected, with an estimated standard deviation of 20. A sample size of 24 participants (12 in each treatment arm) is then required to achieve a power of 80% for two-sided testing at a 5% significance level.

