## Assignment of interventions: allocation

### Sequence generation {16a}

The randomization sequence list was computer-generated using the online platform “Sealed envelope” (available at: sealedenveloppe.com). Randomization is generated with a parallel 1:1 allocation of two treatment groups A and B, using random block sizes of 4. No stratification of participant characteristics was implemented.

Independently from the randomization sequence list, the physiotherapist defined randomly groups A and B (TTNS or sham).

Subsequently, the randomization sequence list was exempted for use to the physiotherapist.

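### The plan does not say whether absolute or percentage change in AVV decides superiority, and the deciding comparison leaves baseline AVV unadjusted

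*Protocol article*

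**What the plan says.** All references are to the protocol article.

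- **Abstract, Methods:** "The primary outcome is the percentage difference in average voided volume (AVV) between baseline and after 12 weeks of treatment".
- **Sample size {14}:** the calculation uses the same scale, "a mean difference of 20% in the primary outcome (i.e., percentage difference in AVV between baseline and after 12 weeks", "with an estimated standard deviation of 20" and "a power of 80% for two-sided testing at a 5% significance level". It concludes: "A sample size of 24 participants (12 in each treatment arm) is then required".
- **Primary outcome (under Outcomes {12}):** "The endpoint is the median change in baseline at 12 weeks in AVV, registered on the daytime bladder diary". No scale is given. The opening of Outcomes {12} has every outcome reported as both absolute and percentage change.
- **Statistical methods {20a}:** for the comparison of sham with TTNS, "differences in absolute and percentage change from baseline between both groups will be reported as medians (IQR", with a 95% confidence interval and a two-sided Mann-Whitney U test. Neither scale is marked as decisive and no covariate is included. The stated reason for rank tests is the small sample.
- **Sequence generation {16a}:** "No stratification of participant characteristics was implemented". Eligibility spans ages 5 to 12, and baseline AVV is recorded on a case report form for every child (section {18a}).
- **Dissemination plans {31a}:** part II starts if superiority over sham is proven.

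**The concern.** There are two linked problems.

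First, the sections that govern the analysis do not carry through the scale fixed in the abstract and the sample size. Read alone, the statistical methods produce two between-arm p-values for AVV and no rule for a trial in which one is below 5% and the other is not. That result decides whether part II goes ahead.

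Second, both comparisons use change scores with no baseline covariate. Bladder volume can be expected to vary widely between ages 5 and 12, and with 12 unstratified children per arm a chance difference in baseline AVV is likely. A change score removes only part of such a difference. The rest sits in the treatment estimate as noise that a measured covariate could remove.

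**Working it through.** **1. The plan's own sample size.** Inputs: difference 20, SD 20, two-sided 5%, power 80%.

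n per arm = 2 × (1.960 + 0.842)² × (20/20)² = 2 × 7.849 = 15.7, so 16 per arm or 32 in total (17 per arm by t-test). The stated 12 per arm is not reproduced. Power at 12 per arm: Φ(√(12/2) − 1.960) = Φ(0.489) = 68.8%, or 64.9% by t-test. This is the starting point for any statement about power.

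**2. How much baseline imbalance carries over.** The baseline-to-follow-up correlation ρ is not in the document, so 0.3 to 0.9 is assumed, with equal log-scale variances at both times. The log change score keeps (1 − ρ) of any imbalance in log baseline. With an SD of the log ratio of 0.20, the SD of log AVV is 0.20/√(2(1 − ρ)). The carried-over imbalance at 12 per arm then has SD 0.20 × √((1 − ρ)/2) × √(2/12):

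- ρ = 0.3: 0.20 × 0.592 × 0.408 = 0.048
- ρ = 0.5: 0.20 × 0.500 × 0.408 = 0.041
- ρ = 0.9: 0.20 × 0.224 × 0.408 = 0.018

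Against a log effect of 0.20, a typical (1 SD) accident is about 24%, 20% and 9% of the effect.

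**3. Simulation.** 10,000 trials per setting, 12 per arm, log-normal AVV, SD of log ratio 0.20, log effect 0.20 (1 SD, as planned), exact Mann-Whitney. Figures are percentages.

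| ρ (assumed) | Mann-Whitney, % change | Mann-Whitney, absolute | The two disagree | t-test on log ratio | Log ANCOVA |
|---|---|---|---|---|---|
| 0.3 | 61.2 | 64.3 | 5.8 | 65.2 | 80.9 |
| 0.5 | 61.2 | 64.0 | 6.1 | 64.9 | 75.1 |
| 0.7 | 60.4 | 63.0 | 7.1 | 64.9 | 69.9 |
| 0.8 | 60.4 | 62.1 | 8.5 | 64.5 | 66.7 |
| 0.9 | 61.6 | 60.2 | 11.1 | 65.2 | 64.9 |

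With no effect, counting either Mann-Whitney test as success rejects in 4.9 to 5.5% of trials, against 4.2 to 4.6% for percentage change alone. Two independent tests would give 1 − 0.95² = 9.75%. Log ANCOVA rejects in 4.7 to 5.3%.

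**4. Where the gain comes from.** About 4 points come from replacing the rank test with a parametric test (column 5 minus column 2). Adjustment itself (column 6 minus column 5) adds about 16, 10, 5, 2 and 0 points.

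**5. When the model is wrong.** The same design was rerun (20,000 trials per setting) with non-normal follow-up residuals scaled to the same variance. With t residuals on 3 degrees of freedom, Mann-Whitney on percentage change against log ANCOVA gives 72% v 85% at ρ = 0.3, 78% v 78% at 0.7 and 81% v 74% at 0.9. With exponential residuals it gives 69% v 81%, 75% v 73% and 79% v 69%. The gain is gone or reversed from about ρ = 0.7.

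**6. What the log-scale estimate means.** If sham does not change, a 20-point difference is 120/100 = 1.20. If sham rises by 20%, it is 140/120 = 1.17. If the planned effect is taken as a ratio of 1.2 (log 0.182), power at 12 per arm is 57 to 73% for ANCOVA and 52 to 53% for Mann-Whitney on percentage change.

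**The case against.** The strongest reply is that the primary scale is named, twice, and that the response categories in Study schedule are also percentage increases. Giving both scales is then a reporting format, and section {20a} is one generic paragraph for all outcomes. This stands in part: a reader might infer that the primary outcome is undefined, and the document does not support that. What remains is that the Primary outcome and statistical methods sections do not carry the choice through.

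Three further inferences also go too far.

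- **Two scales seriously inflate type I error.** The tests are highly correlated and the inflation is about 1 point.
- **The analysis ignores baseline.** Percentage change divides by baseline and ranks children exactly as the log ratio does. What is absent is adjustment for baseline as a covariate.
- **ANCOVA restores the stated 80% power.** In simulation with 24 children it does so only at ρ of about 0.3. Most of the shortfall comes from having 24 children where about 32 are needed.

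It is also fair to say that the Mann-Whitney test is valid, that the reason given for it (small sample) is a recognised one, and that the favourable simulation was drawn from the model that ANCOVA assumes. The non-normal runs confirm that the advantage is conditional. For that reason the rank test should be kept as a prespecified check. How rank results would be pooled after multiple imputation is detail that an analysis plan commonly settles, so it is not counted here.

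**Conclusion.** The point holds in this form. The sections governing the analysis leave open which of two AVV comparisons decides superiority. At the planned effect that matters in about 6 to 11% of simulated trials, and the cost is an unclear verdict, with little excess false-positive risk. Separately, a baseline measured on every child is not adjusted for in a small unstratified trial. Adjustment takes power at 12 per arm from about 60% to 81, 75, 70, 67 and 65% at ρ of 0.3, 0.5, 0.7, 0.8 and 0.9.

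The direction of the power result rests on assumptions outside the document: the correlation, equal log-scale variances and roughly normal log-scale residuals. The scale ambiguity rests on the text alone.

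**What to change.** 1. In the Primary outcome section and in section {20a}, state that one relative-scale analysis decides superiority and that absolute change in AVV is descriptive.
2. Make that analysis an ANCOVA of log(12-week AVV) on arm and log(baseline AVV), two-sided 5%, reported as a ratio of geometric means with 95% confidence interval.
3. Keep Mann-Whitney on percentage change as the prespecified sensitivity analysis, to show whether the conclusion depends on the residual assumption.
4. Reword the endpoint as a ratio and restate the planning effect on that scale. It equals the 20-point difference only if sham does not change, and both arms receive urotherapy.
5. Correct the stated sample size or power separately. Under the same log-normal model, 16 per arm gives ANCOVA power of 88, 84 and 81% at ρ of 0.5, 0.7 and 0.8, against about 75% for Mann-Whitney on percentage change.

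Items 1 to 4 need no extra visits or data and one regression in the software already named. The cost is more than a wording change, because the estimand moves from a median change to a ratio and recruitment is already under way. The change should therefore be a dated amendment made before the research assistant is unblinded. If the sponsor prefers to keep the rank test as primary, item 1, with percentage change as the decisive scale, is the minimum.

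### The between-arm effect is specified as medians (IQR) with a 95% interval that nothing ties to the Mann-Whitney test; name the Hodges-Lehmann shift with its test-inversion interval

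*Protocol article*

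**What the plan says.** All references are to the protocol article.

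- **Statistical methods {20a}, reporting:** differences in absolute and percentage change "between both groups will be reported as medians (IQR) and will be presented with a 95% confidence interval".
- **Statistical methods {20a}, test:** "Inter-arm analyses will be assessed using a two-sided the Mann-Whitney" U test. The reason given is "Since the small sample size, non-parametric tests will be chosen".
- **Outcomes {12}:** every outcome is summarised as a median (IQR) change from baseline, both absolute and percentage.
- **Primary outcome:** "The endpoint is the median change in baseline at 12 weeks in AVV".
- **Sample size {14}:** the trial is powered on "a mean difference of 20% in the primary outcome", "with an estimated standard deviation of 20". "A sample size of 24 participants (12 in each treatment arm) is then required".

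The article does not say which between-arm quantity the interval covers or how it is computed. It mentions neither a Hodges-Lehmann estimate nor a median of pairwise differences.

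**The concern.** The reporting sentence merges two things. A median with an IQR describes the changes of the children in one arm. The contrast between two independent arms is a single estimate with an interval, and it has no IQR.

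Once the IQR is set aside, the sentence still leaves the contrast undefined. The outcome sections speak only of arm-level medians, so an analyst would most plausibly subtract one median from the other and put an interval on the result. Mann-Whitney works on all TTNS-sham pairs. It can be significant when the medians are close, and not significant when they are apart. An interval for the difference of medians can therefore include zero beside p < 0.05, or exclude it beside p > 0.05.

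At stake is a primary result that readers could take two ways, with an effect estimate that is usually less precise than the data allow. The same sentence governs the secondary outcomes.

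**Working it through.** **Inputs.** 12 per arm, difference 20 points in percentage change, SD 20, two-sided 5% (Sample size {14}); Mann-Whitney test (statistical methods {20a}). *Assumed, because the article names none:* the distribution shape and the method for a difference-of-medians interval.

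**The plan's own figure.** n per arm = 2(z₀.₉₇₅ + z₀.₈₀)² × SD²/Δ² = 2(1.960 + 0.842)² × 20²/20² = 15.7, so 16 per arm (32 in total), against the stated 24. The stated size does not reproduce. That is a separate matter; I keep 12 per arm here because that is what will be analysed.

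**Test.** For 12 against 12 the exact two-sided test rejects when the smaller U ≤ 37, with an actual level of 0.0449.

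**Interval that belongs to the test.** Form all 12 × 12 = 144 TTNS-minus-sham differences. The Hodges-Lehmann estimate is their median, and the interval runs from the 38th smallest to the 38th largest. Its lower limit exceeds zero exactly when at most 37 of the 144 differences are zero or negative, which is the rejection rule U ≤ 37. The upper limit works the same way. Without ties, test and interval cannot disagree.

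**Interval for the difference of medians.** Two versions:

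- percentile bootstrap, 600 resamples;
- Price-Bonett type. Each arm has SE = (x₍₁₀₎ − x₍₃₎)/(2 × 2.069), where 2.069 is the normal quantile at 1 − (1 + 12 + 66)/4096. The interval is the median difference ± 1.96 × √(SE₁² + SE₂²).

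**Simulation, 5,000 trials per row, shift 20, SD 20.** Mean widths in percentage points; the percentage in brackets is the excess over Hodges-Lehmann.

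| Shape | Hodges-Lehmann width | Bootstrap width | Price-Bonett width | Bootstrap disagrees with test | Price-Bonett disagrees with test |
|---|---|---|---|---|---|
| Normal | 35.4 | 40.0 (+13%) | 43.6 (+23%) | 13.8% | 21.9% |
| Skewed (lognormal) | 27.1 | 32.5 (+20%) | 35.3 (+30%) | 12.8% | 21.7% |
| t, 3 df | 26.6 | 27.7 (+4%) | 30.8 (+16%) | 7.7% | 15.9% |
| Laplace | 30.9 | 31.6 (+2%) | 35.6 (+15%) | 9.6% | 19.2% |

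Hodges-Lehmann disagreed with the test in 0% of trials in every row. For normal data the bootstrap disagreement of 13.8% splits into 11.8% with a significant test and an interval including zero, and 2.0% the other way. The simulation error on 13.8% is about √(0.138 × 0.862/5000) = 0.5 points.

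**With no true effect (shift 0).** Disagreement is 2.3-2.6% with the bootstrap and 3.9-4.2% with Price-Bonett.

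**Are the two quantities different?** Under a pure shift of 20 both equal 20, so the table shows a difference in precision and agreement, not in what is estimated. They separate when the effect is uneven. Suppose 40% of treated children gain 60 points, the rest gain nothing, and the SD is 20:

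- difference of medians: 0.6Φ(m/20) + 0.4Φ((m − 60)/20) = 0.5 gives m = 18.4;
- median pairwise difference: the same equation with 20√2 in place of 20 gives 21.4.

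**The case against.** The strongest reply is that the text fixes no mismatch. A difference reported as a median with a 95% interval could mean the median of the pairwise differences, which is the Hodges-Lehmann estimate. The method for an interval is also a detail that a journal article may leave to the full protocol or analysis plan. This stands in part. A reader might infer that the planned interval is known not to belong to the test, and the article does not support that. The complaint is not mere silence, however. The article does write a reporting rule, attaches an IQR to a between-arm difference, and surrounds it with arm-level medians.

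A reader might also infer that the interval will always be appreciably wider than necessary. It will not: with heavy-tailed data and a bootstrap the excess is only 2-4%.

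A third tempting inference is that the decision on part II is left with two competing answers. The Dissemination plans {31a} launch part II if superiority is proven, and {20a} assigns the between-arm assessment to Mann-Whitney. The test decides; an inconsistent interval would confuse the report, not change the decision rule.

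Finally, exact agreement does not carry over everywhere. The 7-point Likert score and the episode counts will be heavily tied, and multiple imputation is planned ({20a}, {20c}). Pooling over imputed data sets does not invert one exact test. This objection stands and limits what the fix can promise.

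**Conclusion.** The concern holds as a defect of specification: an IQR is attached to a between-arm difference, and the 95% interval is not tied to the test beside it.

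Its size depends on taking the interval to be for the difference of arm medians, which is the natural reading but not a stated one. On that reading, at 12 per arm, shift 20 and SD 20, a bootstrap interval is about 2-20% wider than Hodges-Lehmann over the four shapes tried, and it disagrees with the test in about 8-14% of trials. The Price-Bonett version does worse on both counts. With no effect, disagreement is about 2-4% over the two methods.

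The figures rest on complete, continuous data and a pure shift. What is affected is the reported effect and its precision, not the error rate, the power or the sample size. It is worth correcting because a clearly better method is available at almost no cost.

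**What to change.** In statistical methods {20a}, replace the inter-arm reporting sentence with wording to this effect:

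- Changes within each arm are described as median (IQR).
- For the primary outcome, the between-arm effect is the Hodges-Lehmann shift (the median of all pairwise TTNS-minus-sham differences), with the 95% interval obtained by inverting the Mann-Whitney test.
- For tied secondary outcomes (Likert score, episode counts), the tie-adjusted or asymptotic version is used.
- Where data are multiply imputed, the estimates are pooled across imputations. Exact agreement of interval and test is claimed only for complete, continuous data.

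Align the Primary outcome wording, so that the median change describes each arm and the shift is the comparison between arms.

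The cost is a few sentences of analysis text and a line explaining the shift estimate to readers. No patients are added, trial conduct does not change, and Mann-Whitney stays the decision rule.
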